#### Standard of care (SOC)

In facilities allocated to the SOC arms, health facilities will provide HIV testing and ART initiation as dictated by national guidelines. In Malawi, pre-existing reproductive health CBDAs will continue providing services in standard of care areas.

### Trial participants and procedures

The trial flow charts (Figs. 1 and 2) illustrate the recruitment processes used during the two CRTs. In Malawi, all clinics offering ART in the study districts were eligible for inclusion. In Zambia, there were 109 clinics in four districts where HIVST would be distributed. Clinics hosting other HIV-related programs or that did not offer ART were not eligible for inclusion. Clinics were matched based on size of population served and, for peri-urban sites, distance from urban centre.

**Fig. 1 Fig1:**
[figure not shown]
Flow chart, HIV STAR-Malawi

**Fig. 2 Fig2:**
[figure not shown]
Flow chart, HIV STAR-Zambia

### Data collection

Repeated cross-sectional surveys will be used to evaluate the effectiveness of the intervention. Household survey data will be collected at baseline, before the intervention starts, and after at least 12 months of intervention delivery. Household surveys also include DCEs and questions on costs of testing for use in economic analyses. Contents of the baseline and endline surveys are online at: http://hivstar.lshtm.ac.uk/protocols/). In addition, process data on the number of tests distributed and used will be collected from individuals accepting HIVST by CBDAs and in questionnaires completed by clients themselves. Qualitative data will be collected for formative research and process evaluations. Table 4 provides an overview of data collected for the STAR-Malawi and STAR-Zambia impact evaluations.

**Table 4 Tab4:** Overview of data collected for HIV STAR-Malawi and HIV STAR-Zambia impact evaluations

Data type	Data collected		
	Pre-intervention	During intervention period	12 months after intervention begins
Household survey	• Ever tested • Tested within past 12 months • Current ART use • Self-reported circumcision status		• Ever tested • Tested within past 12 months • Current ART use • Self-reported circumcision status
Clinic data extraction	ART initiations from each study clinic by sex, age, self-testing status		
CBDA M&E data		• Number of kits distributed • Sex and age of persons receiving kits • Barcode on test kit to link with returned kit	
Client-returned kit		• Used test kit • Self-completed questionnaire with test result, client sex, age • Barcode linking to CBDA M&E data	
Qualitative data	• Situational analysis and community mapping (ZM, MW) • Cognitive interviewing on IFUs (ZM, MW) • Formative research on attitudes and preferences toward self-testing (ZM)	• Process evaluation (ZM)	
Economics data	• DCEs to understand preferences for testing and linkage • Costs of health facility based HIV testing at baseline		• Costs of HIV testing, including self-test distribution models

#### Malawi – Survey data collection

Evaluation data will be collected from selected villages within the implementation area of each clinic (Fig. 3**)**. Eligibility requirements for the evaluation villages will include:Location within the catchment area of an eligible ART clinic, with the clinic acting as the most dominant source of ART for the village.Presence of at least one active reproductive health CBDA prior to the study period.Population of at least 250 adults per village.Road access for most/all of the year.Sufficient distance and separation from administrative boundaries and other intended evaluation villages to minimise contamination between HIVST and control villages and missed linkage events from seeking HIV care at a clinic not included in the evaluation.Village delineation by natural boundaries (e.g., rivers, roads, forests, etc.)

**Fig. 3 Fig3:**
[figure not shown]
Diagram of Malawi clinic area

Within evaluation villages, all households will be enumerated and a variable fraction will be surveyed to ensure that approximately 300 individuals within households will be included. Within selected households, all eligible household members ages 16 years and older will be surveyed with a short questionnaire including sociodemographic, testing, and sexual behaviour, and 20% of surveyed individuals will receive an extended questionnaire with added questions on HIV care and questions for economic evaluation. Baseline and endline surveys will be administered in different communities within each clinic catchment area.

#### Zambia – Survey data collection

Evaluation data will be collected from an area outlined using a radius of approximately 3.8 km around a central point within the intervention and control areas. Within this area, blocks of 20–30 households will be defined using mapping software and numbered in a spiral sequence. Blocks to be visited at baseline will be determined using a random number generator. Within each randomly selected block, all households will be visited and all eligible household members ages 16 years and older asked to participate in the household survey. An independent sample of blocks will be generated for the baseline and endline surveys.

### Power calculations for survey data

#### Malawi

The survey sample size was calculated to ensure sufficient power to identify a difference in the primary outcome between the HIVST intervention and standard care arms for the first stage randomization. The calculation accounts for clustering by incorporating the cluster coefficient of variation (*k*) using methods outlined in Hayes and Moulton [18]. The average cluster size was estimated to be 250–500 individuals, which is the typical size of a rural village based on previous experience working in Malawi, and a sample of 250 participants per cluster was used for the sample size calculations. We assume that the cluster coefficient of variation (*k*) was 0.25. Using 2010 Demographic and Health Surveys (DHS) data, the baseline proportion of adults tested in the last 12 months was estimated at 25% to 40% and ever tested at 42% to 60%. Using these assumptions, 11 clusters per arm will allow us to have 80% power to detect a 30% relative difference in recent HIV testing and a 45% relative difference in lifetime HIV testing between arms of the first stage randomization with α = 0.05.

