### Study objectives

The overall objective of these trials is to evaluate the effectiveness of distribution of oral-fluid HIVST kits by community-based distribution agents (CBDA) on uptake of HIV testing, including coverage of recent (within 12 months) and lifetime testing among the population ages 16 years and older, and on ART initiation. The Zambia study also assesses the impact of self-testing on men’s circumcision status, and the Malawi study evaluates differences between arms in linkage to ART (offered routinely under a “test-and-start” strategy by the Government of Malawi) through extraction of clinic-level ART initiation data. Formative research, consisting of qualitative studies and discrete choice experiments (DCEs), will inform the final intervention design, training materials, social harms definitions. Procedures for reporting social harms related to the intervention are informed by qualitative research in each setting. Qualitative research and DCEs will also be used to maximise preferences for service configurations offered for testing and linkage, and to understand participant experiences. Costing studies and a cost-effectiveness analysis of the interventions will also be conducted.

Specific hypotheses tested by the trials include that community-based distribution of HIVST kits will increase:the proportion of the population who have tested for HIV within the past 12 months;the proportion of the population who have ever tested for HIV;the rate of ART initiations in clinics serving populations that received HIVST distribution.

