### Study design

Using a parallel arm design, clinics will be randomly allocated either to receive community-based HIVST distribution in a defined catchment area, or to continue with usual clinic-based HTS (standard of care [SOC]). Clinic catchment areas will be randomized rather than individual testers because the intervention was designed to be delivered by community-based distributors. Individual-level randomization would therefore be inappropriate.

In Malawi, 22 rural primary health clinics will be randomized 1:1 to receive the HIVST intervention or SOC. Within the HIVST intervention arm, CBDAs will also be randomized 1:1 to provide either referrals to home-based ART initiation or the usual referrals to the clinic. Each clinic will contain a pre-defined, concentrated area of implementation, with two villages in each area selected for the baseline and endline household surveys, respectively.

In Zambia, 12 primary health clinics in 4 districts will be pair-matched within districts by distance to the district medical office and catchment area population, and randomized 1:1 to provide the HIVST intervention or SOC.

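### Malawi: 11 clusters per arm give about 58–61% power for a 30% relative increase in recent testing, not the stated 80%; the increase detectable at 80% power is about 40%

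*Protocol article*

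**What the plan says.** The Malawi part of the section on power calculations for survey data sizes the first-stage comparison, whose primary outcome is HIV testing in the past 12 months. It uses the between-cluster coefficient of variation: "We assume that the cluster coefficient of variation (*k*) was 0.25". On cluster size, "a sample of 250 participants per cluster was used for the sample size calculations". The baseline proportion recently tested is put at 25% to 40%, the proportion ever tested at 42% to 60%, and α at 0.05. From these it concludes that "11 clusters per arm will allow us to have 80% power to detect a 30% relative difference in recent HIV testing", and also "a 45% relative difference in lifetime HIV testing between arms of the first stage randomization".

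Other sections complete the picture. Under Study design, "22 rural primary health clinics will be randomized 1:1 to receive the HIVST intervention or SOC", so there are 11 clusters per arm. The Randomization section describes restricted randomisation for Malawi, without matching. The hypotheses under Study objectives fix the direction: "community-based distribution of HIVST kits will increase" testing. The section on Malawi survey data collection plans a slightly larger sample in the evaluation villages than the calculation used: "a variable fraction will be surveyed to ensure that approximately 300 individuals within households will be included".

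**The concern.** The power sentence says it follows from the listed assumptions, and those are complete enough to check it. It does not follow. For the increase the trial hypothesises, the power is about 20 percentage points below the stated figure.

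The sentence is also inconsistent within itself. It gives a detectable relative difference of 30% for recent testing and 45% for lifetime testing, although lifetime testing has the higher baseline. With one k and one cluster size, the detectable relative increase cannot be larger for the outcome with the higher baseline.

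This is the power statement for the primary outcome. Under the stated inputs, a true 30% increase would be missed about four times in ten, not two in ten. A reader of a null or imprecise Malawi result who trusted the stated figure would overestimate what that result rules out.

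**Working it through.** **Inputs.** c = 11 clusters per arm, m = 250, k = 0.25, p0 = 0.25 to 0.40 and α = 0.05, all from the Malawi power paragraph. The direction (increase) comes from Study objectives. The sidedness of α is not stated; two-sided is assumed, and one-sided is tried below.

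**Formula** (unmatched, coefficient-of-variation form):

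c = 1 + (z_α/2 + z_β)² × [p0(1−p0)/m + p1(1−p1)/m + k²(p0² + p1²)] / (p1 − p0)²

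with (1.960 + 0.842)² = 7.849 for 80% power. For fixed c, power = Φ(|p1 − p0| × √((c − 1)/V) − 1.96), where V is the bracketed variance.

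**Looking for the plan's figure of 11.** The pair 25% and 17.5% matches it:

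- V = 0.001327 + 0.005820 = 0.007148
- c = 1 + 7.849 × 0.007148 / 0.005625 = 10.97, with 80.1% power at 11 clusters

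That is either a 30% reduction from 25%, contrary to the hypothesis, or a 43% rise (0.25/0.175 = 1.43) from a control rate below the stated range.

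**A 30% increase over the stated baseline.**

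- 25% to 32.5%: V = 0.001628 + 0.010508 = 0.012135. c = 1 + 7.849 × 0.012135 / 0.005625 = 17.93. Power at 11 = Φ(2.153 − 1.96) = 57.7%.
- 32.5% to 42.25%: c = 17.19; power 59.5%.
- 40% to 52%: V = 0.001958 + 0.026900 = 0.028858. c = 1 + 7.849 × 0.028858 / 0.0144 = 16.73. Power at 11 = Φ(2.234 − 1.96) = 60.8%.

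**Increase detectable at 80% power with 11 per arm.** The ratio is 1.409 at p0 = 25% (to about 35.2%) and 1.392 at p0 = 40% (to about 55.7%).

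**Variants for the 30% increase, 11 clusters per arm.**

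| Variant | Power |
|---|---|
| Noncentral t, 20 df | 57.5–60.6% |
| Log scale, t | 58.4–61.6% |
| Without the added cluster (the "+1") | 61.7–64.9% |
| m = 300 | 58.6–61.3% |
| m = 500 | 60.6–62.3% |
| Unlimited sampling per cluster | 63.8% |
| One-sided α = 0.05 | 69.4–72.2% |
| One-sided, without the +1 | 73.0–75.7% |
| Equal between-cluster SD in both arms | 68.5–72.6% |
| Equal SD, without the +1 | 72.6–76.6% |

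None reaches 80%. The unlimited-sampling row shows that between-cluster variation is the limit, so surveying more people per village cannot close the gap. With the formula as written, k would have to be about 0.18 to 0.20 for the claim to hold.

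**Lifetime testing, 45% increase.**

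- 42% to 60.9%: c = 8.94; power 88.2%.
- 60% to 87%: c = 8.67; power 89.2%.
- Ratio detectable at 80% power: 1.391 at 42% (to about 58.4%) and 1.382 at 60% (to about 82.9%).

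Reading both effects as reductions does not reconcile the sentence: a 45% reduction in lifetime testing (42% to 23.1%, or 60% to 33%) would need only 4.5 or 4.4 clusters.

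**Why the ordering is wrong.** Put p1 = r × p0 and divide the formula through by p0². The between-cluster part becomes k²(1 + r²)/(r − 1)², which does not depend on p0. The sampling part becomes [(1/p0 − 1) + (r/p0 − r²)]/[m(r − 1)²], which falls as p0 rises. A higher baseline therefore cannot need a larger relative increase.

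**The case against.** The strongest reply is that the text says relative difference without naming the reference arm. If the 30% is taken relative to the intervention arm, the ratio over control is 1/0.7 = 1.43. Power is then 82.9% at a 25% control rate and 85.4% at 40%. That reading keeps the hypothesised direction and the stated control range. It may explain where the figure came from, and it means a reduction is not the only possible source. But the protocol does not say it, and it amounts to a 43% increase over control. A reader who takes the 30% in the usual way is still misled.

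Second, restricted randomisation and the covariate-adjusted primary analysis may lower the effective between-cluster variation. That is possible, but the protocol does not quantify a gain, and the power paragraph calculates at k = 0.25. What stands is that 58–61% is the power under the stated inputs, not necessarily the power the trial achieves.

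Third, the lifetime figure is conservative and concerns a secondary outcome, so it harms no inference. That is fair. It matters mainly as a sign that the two figures were not produced from one consistent calculation.

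Fourth, allocation was completed in 2016 and the design cannot change. This bears on the remedy, not on whether the statement is correct.

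**Conclusion.** The stated power is wrong as written. With 11 clusters per arm, 250 per cluster, k = 0.25 and a control proportion of 25% to 40%, a 30% relative increase in recent testing has about 58–61% power at two-sided 5%. Reaching 80% would take 17 to 18 clusters per arm, and the increase detectable at 80% power with 11 is 39–41%. The lifetime figure errs the other way: a 45% increase has 88–89% power, and the detectable increase is 38–39%.

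These results assume that the 30% is measured over the control rate, that k is the same in both arms and for both outcomes, and that the test is two-sided. Relaxing the sidedness, or holding the between-cluster SD equal across arms, raises the power for recent testing to at most 76.6% among the variants tried.

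**What to change.** Restate the Malawi power paragraph:

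- Give the direction of effect, the reference arm, the rates in both arms and the sidedness of alpha.
- State that 11 clusters per arm with k = 0.25 and 250 per cluster give 80% power for a relative increase of about 40% in recent testing (25% to about 35%, or 40% to about 56%) and about 39% in lifetime testing (42% to about 58%, or 60% to about 83%).
- State that power for a 30% increase in recent testing is about 58–61%.
- If the original calculation used a different reference arm or a smaller effective k, say so and show the inputs, so that the figure can be reproduced.

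No clusters need to be added, and the randomisation, survey and analysis stay as they are. The cost is corrected text and a less favourable detectable difference.

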#### Zambia

As in Malawi, the survey sample size was calculated to ensure sufficient power to identify a difference in the primary outcome between those receiving the HIVST intervention and those receiving standard care, and uses similar methods. We estimated that the cluster coefficient of variation (k) was 0.2, and that cluster populations were larger than in Malawi. Using 2013–2014 DHS data, baseline rates for adults tested in the last 12 months is estimated to be between 28.6–57.1% (lower in men than women). For this sample calculation, we will assume a testing rate of 50% in the standard of care arm. For a two-sample comparison of matched proportions across 6 pairs of matched communities, we will have 80% power to detect a 50% relative difference in recent HIV testing if we recruit around 400 respondents per community, or 4800 respondents in total.

### Randomization

The Malawi trial includes two stages of randomization. In the first stage, clinic catchment areas will be allocated to HIVST or standard of care arms using restricted randomization. To ensure that intervention and standard of care clinics are evenly distributed geographically across the study area, we will restrict the number of intervention clinics in each district, with larger districts to include at least 35% intervention clinics. We will balance arms in terms of number of testers, proportion of positive tests, and total catchment population across clinics. The study statistician (MN) provided a list of 1000 eligible randomization combinations to the study team and the final randomization scheme was selected in a public ceremony in Blantyre, Malawi on 21 March 2016.

In the second-stage randomization, we will randomize all CBDAs providing HIVST to home-based initiation of ART or standard of care at a 1:1 ratio. CBDAs will be randomized in blocks of varying sizes from 2 to 12 CBDAs, with the distribution of block sizes following Pascal’s triangle (i.e., 1:5:10:10:5:1).

In Zambia, clinics will be randomized 1:1 within matched pairs to receive the HIVST intervention or standard of care. Randomization was conducted by the statistician (BH) and was completed on 24 June 2016.

### Outcome evaluation and measurement

#### HIVST intervention

The primary outcome of the HIVST evaluation in both Malawi and Zambia is the proportion of village residents (16 years and above) who tested for HIV within 12 months after the beginning of the intervention period. Outcome data (numerators and denominators) will be collected during an endline household survey.

Secondary outcomes for the Malawi study include the proportion who report ever HIV testing, and the proportion initiating ART at clinics for participant residents in evaluation areas during months 1 to 12 of intervention. Outcome data (numerators and denominators) for ever testing will be collected during an endline household survey. ART initiation data will be extracted from clinic records at 3-month intervals, and the allocation status of each individual in the clinic records will be ascertained using the client’s village of residence. Denominator data will be village adult population counts.

Secondary outcomes for the Zambia study include reported HIV testing during the intervention period, reported lifetime testing for HIV, self-reported current ART use, ART initiation, and self-reported recent circumcision for men. Data to measure these HIV testing, current ART use, and recent circumcision will be collected in the household endline survey. ART initiation will be measured using routine facility data on ART initiations.

#### Malawi – Home-based ART intervention

The primary outcome for the second-stage randomisation of CBDAs to home-based initiation or clinic referral will be the number of participants (16 years and older) disclosing a positive result to the CBDA during months 1 to 12 of the intervention. Status disclosure is captured through returned self-completed questionnaires by the CBDAs.

The secondary outcome for this second-stage randomisation will be ART initiation rates for participants (16 years and older) during months 1 to 12 of intervention. Data to measure ART initiation will be collected in two different ways: for the HIVST testing intervention, data will be extracted from routine facility ART records as for Zambia. For the home-initiation versus facility-initiation linkage intervention, ART initiations will be identified through collection of “self-referral forms” provided to all clients that include CBDA identification information and data on the type of HIV care received. In the SOC arm, self-referral forms will be collected from health facilities. In the home-based-initiation arm, self-referral forms are collected from health facilities or the study nurse providing HIV care at home. Counts of self-referral forms will be compared to calculate differences in ART uptake across arms.

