### Intervention and standard of care

Both trials will assess the effectiveness of community-distributed HIVST on HIV testing uptake using OraQuick HIV Self Tests (Bethlehem, PA USA, assembled in Thailand) including instructions-for-use translated by the manufacturer into local languages (Chichewa in Malawi; and Nyanja, Tonga, and Bemba in Zambia). The specificity and sensitivity of the test kit in a general rural population in sub-Saharan Africa will be assessed in separate studies [16]. HIVST kits will be stored and distributed by Population Services International (PSI)-Malawi or Society for Family Health (SFH)-Zambia. In both trials, CBDAs will be trained by PSI or SFH in how to explain the written self-test instructions, demonstrate correct use, and show examples of reactive and non-reactive tests to assist in reading results. Distributors will also be trained on appropriate test kit storage and information concerning linkage to confirmatory testing and ART for clients with reactive HIVST results or prevention for clients with non-reactive results. Clients will be offered the choice of testing with CBDA assistance or in private. CBDAs will also be trained in how to pre-empt, respond to and report social harm, including suicide, gender-based violence, or coerced testing. Individuals are eligible for HIVST if they are ages 16 years or older.

In Malawi, CBDAs will provide door-to-door community-based distribution of HIVST kits as well as access from their own homes, building on a pre-existing initiative providing reproductive health products. CBDAs will provide all clients who wish to test with: (1) information on the test and a demonstration on how to open and use the HIVST kit; (2) an envelope and short anonymous questionnaire to be completed by the client and returned with the kit; and (3) a self-referral form to facilitate linkage into HIV care and prevention services. CBDAs will distribute one test per resident who is interested in testing. CBDAs will visit clients after distributing the kit to enquire whether the kit has been used, collect the sealed questionnaire and used kit, and provide advice on referral to additional care if the client discloses a reactive HIVST result. Clients will also be able to drop used kits in locked boxes within each community, or return them to CBDAs at their homes.

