#### Zambia – HIVST intervention

In Zambia, multiple modes of HIVST distribution will be provided to the catchment population of each intervention facility in addition to a similar CBDA model to Malawi. Healthcare workers will distribute HIVST within health facilities, while CBDAs will visit households to dispense HIVST kits. Voluntary male medical circumcision (VMMC) mobilizers employed by PSI are associated with some but not all facilities, and in intervention areas will distribute self-test kits as part of their activities. Distribution modes for each clinic are listed in Table 3. As in Malawi, clients who agree to HIVST will receive a demonstration of kit use; an envelope for the used kit and anonymous self-complete questionnaire to return with kit; and a self-referral card to the health facility to assist with linkage to confirmatory testing and care as needed. Boxes to return used self-test kits will be located at each facility as well as in public areas in the community, and used kits can be returned to CBDAs.

**Table 3 Tab3:** Primary and secondary outcomes of HIV STAR-Zambia and HIV STAR-Malawi impact evaluations

Outcome	Trial	Data source
Primary outcome – community HIVST distribution		
Tested for HIV within past 12 months	Malawi, Zambia	Self-report, endline household survey
Secondary outcomes – community HIVST distribution		
Ever tested for HIV	Malawi, Zambia	Self-report, endline household survey
ART initiation 6 months and 12 months after distribution begins	Malawi, Zambia	Routine data extracted from clinic
Current ART use	Zambia	Self-report, endline household survey
Circumcision within past 12 months (men only)	Zambia	Self-report, endline household survey
Primary and secondary outcome – home-based distribution (Malawi only)		
Primary: Disclosure of a positive results to the CBDA during months 1 to 12 of intervention	Malawi	CBDA post-test log book
Secondary: ART initiation between months 1 and 12 of the intervention	Malawi	Routine data extracted from clinic

CBDAs will be recruited from the communities in which they will work, and will have previously worked with the health facilities included in the impact evaluation. CBDAs and VMMC mobilisers will be paid using a performance-based structure (ZMW 5/distributed kit and ZMW 2.5/used kit returned, or USD 0.56 and 0.28).

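### Malawi second-stage randomisation: Table 3 and the outcome text name conflicting data sources for both outcomes, and the form count of ART starts may be unequally complete between sub-arms

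*Protocol article*

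**What the plan says.** The second-stage comparison is set up in the Randomization section: "we will randomize all CBDAs providing HIVST to home-based initiation of ART or standard of care at a 1:1 ratio". Standard of care here means clinic referral within the HIVST catchment areas, not the first-stage control clinics.

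*Primary outcome (disclosure of a positive result to the CBDA, months 1 to 12).* Table 3 gives the source as "CBDA post-test log book". Outcome evaluation and measurement, under Malawi – Home-based ART intervention, says instead: "Status disclosure is captured through returned self-completed questionnaires by the CBDAs". Intervention and standard of care describes that questionnaire as part of "an envelope and short anonymous questionnaire to be completed by the client and returned with the kit". The CBDA's later visit is to "collect the sealed questionnaire and used kit", and used kits may also be left in locked community boxes.

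*Secondary outcome.* Table 3 lists "Secondary: ART initiation between months 1 and 12 of the intervention" with routine clinic extraction as its source. The outcome text reserves routine facility records for the first-stage HIVST comparison. For home against facility initiation it identifies ART starts by self-referral forms that carry CBDA identification. On collection it says: "In the SOC arm, self-referral forms will be collected from health facilities". It then says: "In the home-based-initiation arm, self-referral forms are collected from health facilities or the study nurse providing HIV care at home". The numbers of forms are then compared between arms.

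**The concern.** Each outcome of this randomisation has two stated sources, and in each case the two do not measure the same thing.

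For the primary outcome, confiding in the CBDA and ticking a reactive result on a sealed, anonymous form are different acts. A client can do either without the other. The home-ART offer works through confiding, since the client must tell the CBDA before a nurse visit is arranged. A questionnaire count could miss the effect the offer is meant to produce.

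For ART starts, a clinic start enters the form count only if the client hands in the form and the clinic keeps it. A home start can be captured by the nurse who delivers the care. If those two routes differ in completeness, a comparison of raw counts mixes form handling with ART uptake. Leaving the source open also allows it to be chosen after the data are seen.

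**Working it through.** The article gives no sample size, rate or power for the second stage, so there is no figure to reproduce. The check sets the texts side by side and then works an illustration.

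**1. Sources side by side**

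| Outcome | Table 3 | Outcome text |
|---|---|---|
| Disclosure to the CBDA | CBDA log book | Client questionnaires |
| ART initiation | Routine clinic data | Self-referral forms |

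The questionnaire is anonymous, sealed and returned with the kit, possibly through a locked box. Table 4 files its test result under the client-returned kit and links it by barcode to CBDA data. A reactive result can thus be attributed to a CBDA without the client having told that CBDA anything. The documents give no return or disclosure rates, so no size can be put on this part.

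**2. ART starts by form count, no true difference**

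Assumed inputs, none from the documents: h = share of home-arm starts made at home; n = share of home starts whose form the nurse captures; c = share of clinic starts whose form is captured.

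Apparent ratio (home : clinic referral) = [h·n + (1 − h)·c] / c.

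With h = 0.5 and n = 1:
- c = 0.9: (0.50 + 0.45)/0.9 = 1.06
- c = 0.7: (0.50 + 0.35)/0.7 = 1.21
- c = 0.5: (0.50 + 0.25)/0.5 = 1.50

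With h = 0.25 the same values of c give 1.03, 1.11 and 1.25. With h = 0.75 they give 1.08, 1.32 and 1.75. The ratio is above 1 only when n exceeds c. With n = 0.95, c = 1 and h = 0.5 it is (0.475 + 0.5)/1 = 0.975.

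**3. ART starts by clinic register alone (the Table 3 source), no true difference**

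r = share of home starts later entered in a clinic register (assumed), with clinic starts fully registered.

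Apparent ratio = h·r + (1 − h).

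With h = 0.5:
- r = 0.9: 0.45 + 0.5 = 0.95
- r = 0.7: 0.35 + 0.5 = 0.85
- r = 0.5: 0.25 + 0.5 = 0.75

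Under these assumptions the two named sources push the estimate in opposite directions.

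**The case against.** A reader might infer that the two arms' ART starts are counted from different sources. The text does not support that. One form is given to all clients in both sub-arms, and the nurse is an added collection point because home starts take place at home. Without it those starts would be lost. What stands is possible unequal completeness of a single source.

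A reader might also infer that the comparison favours home ART. No capture rate is given for nurse or clinic, so this is conditional: it holds for the form count if nurse capture exceeds clinic capture. If every home-arm start were at home the ratio would be 1/c, or 1.11 to 2.00 for c from 0.9 to 0.5. That is an outer bound, because home-arm forms also come from facilities.

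There is a good reason for using the form. It carries CBDA identification, whereas Table 4 lists clinic extraction only by sex, age and self-testing status. A village needs at least one active CBDA and may have several, so village of residence need not identify the CBDA. This counts against a register-only remedy, which would also miss home starters who never register at a clinic.

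The log book is not neutral either. In the home arm, disclosure triggers a nurse visit, so recording it has a purpose that clinic referral lacks, and CBDAs are unblinded. That calls for identical recording in both sub-arms. It does not rescue the questionnaire, which records a different event.

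**Conclusion.** The concern holds in this form. The article contradicts itself on the source for both second-stage outcomes, and this needs no assumption. For disclosure, the questionnaire named in the text cannot show that the CBDA was told; the Table 3 source matches the stated outcome.

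For ART starts, form completeness may differ by sub-arm. The illustrative distortion with no true difference is 1.06 to 1.50 for the form count and 0.95 to 0.75 for a register-only count. Both ranges assume that half of home-arm starts are at home. The first also assumes full nurse capture and clinic form capture of 90% to 50%. The second assumes that 90% to 50% of home starts reach a register and that all clinic starts do. The actual size and direction cannot be known from the article.

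The point is confined to the second-stage comparison. The main trial outcome, survey-reported testing, is unaffected. The sources should be reconciled before second-stage data are analysed.

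**What to change.** State one ascertainment rule per outcome, in the same words in Table 3 and the outcome text, and apply it to both sub-arms.

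- *Disclosure:* use the CBDA post-test log book, and delete or correct the questionnaire sentence. Confirm that the log has a disclosure entry completed in the same way in both sub-arms, since Table 4 lists none. Questionnaire results can be reported separately as self-reported reactive tests.
- *ART initiation:* count starts from clinic ART registers plus the study nurses' home-initiation records. De-duplicate, because home starters continue care at a clinic. Link each start to a CBDA, using the identification on the self-referral form where available. Report form counts alone as supportive.

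The disclosure change costs only wording. The ART change needs some record linkage; clinic records are already extracted every three months. Some register entries may not be attributable to a CBDA. If attribution depends on the form, that shortfall acts like c in the first formula. Unattributed starts should therefore be reported by clinic, with bounds that assign them to either sub-arm.
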